### **8.8. Pharmacodynamics Analysis**

PD biomarker data, including but not limited to serum ANGPTL3, ApoC3, and markers of DNL (e.g., malonate carnitine index), if applicable, will be listed and summarized using descriptive statistics by cohort and treatment groups at individual sampling time points. Summary statistics may also be provided to characterize the effect of concomitant food intake on the PD biomarkers. Exploratory analyses may be performed to evaluate associations amongst the biomarkers and between the biomarkers and laboratory parameters.

## **8.9. Pharmacokinetics and Pharmacodynamics Analysis**

Dose and/or exposure-response relationships for TLC-2716 with PD biomarkers across all doses will be evaluated, as appropriate.

## **8.10. Sample Size**

Due to its exploratory nature and no reliable variability estimation, no formal power or sample size calculations were used to determine the sample size for this study. Empirically, a sample size of 100-150 subjects (10 subjects per cohort, including 8 active and 2 placebo) was selected to provide an adequate characterization of safety, PK, and PD of TLC-2716.

## **9. RESPONSIBILITIES**

### **9.1. Investigator Responsibilities**

#### **9.1.1. Good Clinical Practice**

The investigator will ensure that this study is conducted in accordance with International Council for Harmonization E6(R2) addendum to its guideline for Good Clinical Practice and applicable laws and regulations.

#### **9.1.2. Financial Disclosure**

The investigator and sub-investigators will provide prompt and accurate documentation of their financial interest or arrangements with the sponsor or proprietary interests in the study drug. This documentation must be provided before the investigator's (and any sub-investigator's) participation in the study. The investigator and sub-investigator agree to notify TLC of any change in reportable interests during the study and for 1 year following completion of the study. Study completion is defined as the date when the last [subject/patient] completes the protocol-defined activities.

#### **9.1.3. Institutional Review Board/Independent Ethics Committee Review and Approval**

The investigator (or TLC as appropriate according to local regulations) will submit this protocol, ICF, and any accompanying material to be provided to the subject (such as advertisements, subject information sheets, or descriptions of the study used to obtain informed consent) to an IRB/IEC. The investigator will not begin any study subject activities until approval from the IRB/IEC has been documented and provided as a letter to the investigator.

Before implementation, the investigator will submit to and receive documented approval from the IRB/IEC for any modifications made to the protocol or any accompanying material to be provided to the subject after initial IRB/IEC approval, with the exception of those necessary to reduce immediate risk to study subject.

#### **9.1.4. Informed Consent**

The investigator is responsible for obtaining written informed consent from each individual participating in this study after an adequate explanation of the aims, methods, objectives, and potential hazards of the study and before undertaking any study-related procedures. The investigator must use the most current IRB/IEC-approved ICF for documenting written informed consent. Each ICF will be appropriately signed and dated by the subject or the subject's legally authorized representative and the person conducting the consent discussion, and also by an impartial witness if required by IRB/IEC requirements.

The ICF will inform subjects about genomic testing and/or planned sample retention. In addition to the study-specific ICF to be signed by each subject participating in the study, subjects will be

required to document additional consent to provide additional samples and/or to allow the use of the remainder of their already-collected specimens for optional future research, in accordance with applicable regulations. In addition to the study-specific informed consent form to be signed by each subject participating in the study, subjects will be required to document additional consent to provide additional samples for optional genomic research. The results of the tests performed on the samples will not be given to the subject or the investigator. The stored biological samples will be destroyed no later than 15 years after the end of the study or per country requirements, but subjects may at any time request that their stored samples be destroyed.

#### **9.1.5. Confidentiality**

The investigator must assure that subjects' anonymity will be strictly maintained and that their identities are protected from unauthorized parties. Only subject initials, date of birth, another unique identifier (as allowed by local law), and an identification code will be recorded on any form or biological sample submitted to the sponsor, IRB/IEC, or laboratory. Laboratory specimens must be labeled in such a way as to protect subject identity while allowing the results to be recorded to the proper subject. Refer to specific laboratory instructions or in accordance with local regulations.

NOTE: The investigator must keep a screening log showing codes, names, and addresses for all subjects screened and for all subjects enrolled in the trial. Subject data will be processed in accordance with all applicable regulations.

The investigator agrees that all information received from TLC, including but not limited to the IB, this protocol, CRF/eCRF, the study drug, and any other study information, remain the sole and exclusive property of TLC during the conduct of the study and thereafter. This information is not to be disclosed to any third party (except employees or agents directly involved in the conduct of the study or as required by law) without prior written consent from TLC. The investigator further agrees to take all reasonable precautions to prevent the disclosure by any employee or agent of the study site to any third party or otherwise into the public domain.

#### **9.1.6. Study Files and Retention of Records**

The investigator must maintain adequate and accurate records to enable the conduct of the study to be fully documented and the study data to be subsequently verified. These documents should be classified into at least the following two categories: (1) investigator's study file, and (2) subject clinical source documents.

The investigator's study file will contain the protocol/amendments, CRF and query forms, IRB/IEC, and governmental approval with correspondence, informed consent, drug records, staff curriculum vitae, authorization forms, and other appropriate documents and correspondence.

The required source data should include sequential notes containing at least the following information for each subject:

- Subject identification (name, date of birth, gender)

- Documentation that the subject meets eligibility criteria (i.e., history, physical examination, and confirmation of diagnosis) to support inclusion and exclusion criteria
- Documentation of the reason(s) a consented subject is not enrolled
- Participation in the study (including study number)
- The study discussed and date of informed consent
- Dates of all visits
- Documentation that protocol-specific procedures were performed
- Results of efficacy parameters, as required by the protocol
- Start and end date (including dose regimen) of study drug, including dates of dispensing and return
- Record of all the AEs and other safety parameters (start and end date, including causality and severity)
- Concomitant medication (including start and end date, dose if relevant, dose changes)
- Date of study completion and reason for early discontinuation, if it occurs.

All clinical study documents must be retained by the investigator until at least 2 years or according to local laws, whichever is longer, after the last approval of a marketing application in an ICH region (i.e., United States, Europe, or Japan) and until there are no pending or planned marketing applications in an ICH region; or, if no application is filed or if the application is not approved for such indication until 2 years after the investigation is discontinued and regulatory authorities have been notified. Investigators may be required to retain documents longer if specified by regulatory requirements, by local regulations, or by an agreement with TLC. The investigator must notify TLC before destroying any clinical study records.

Should the investigator wish to assign the study records to another party or move them to another location, TLC must be notified in advance.

If the investigator cannot provide for this archiving requirement at the study site for any or all of the documents, special arrangements must be made between the investigator and TLC to store these records securely away from the site so that they can be returned sealed to the investigator in case of an inspection. When source documents are required for the continued care of the subject, appropriate copies should be made for storage away from the site.

#### **9.1.7. Case Report Forms**

For each subject enrolled, an eCRF will be completed by an authorized study staff member whose training for this function is documented according to study procedures. eCRF should be completed on the day of the subject visit to enable the sponsor to perform central monitoring of safety data. The Eligibility Criteria eCRF should be completed only after all data related to eligibility have been received and the subject has been enrolled. Subsequent to data entry, a study monitor will perform source data verification within the electronic data capture system.

Original entries as well as any changes to data fields will be stored in the audit trail of the system. Prior to database lock (or any interim time points as described in the clinical data management plan), the investigator will use his/her log-in credentials to confirm that the forms have been reviewed and that the entries accurately reflect the information in the source documents. The eCRF captures the data required per the protocol schedule of events and procedures. System-generated or manual queries will be issued to the investigative site staff as data discrepancies are identified by the monitor or internal TLC staff, who routinely review the data for completeness, correctness, and consistency. The site coordinator is responsible for responding to the queries in a timely manner, within the system, either by confirming the data as correct or updating the original entry and providing the reason for the update (e.g., data entry error). At the conclusion of the trial, TLC will provide the site with a read-only archive copy of the data entered by that site. This archive must be stored in accordance with the records retention requirements outlined in Section 9.1.6.

#### **9.1.8. Study Drug Accountability and Return**

TLC recommends that used and unused study drug supplies be returned to the shipping facility from which it came. The study monitor will provide instructions for return. If return is not possible, the study monitor will evaluate each study center's study drug disposal procedures and provide appropriate instruction for the return and possible destruction of unused study drug supplies. If the site has an appropriate SOP for drug destruction as determined by TLC, the site may destroy used (empty or partially empty) and any unused study drug supplies in accordance with that site's approved SOP. A copy of the site's approved SOP will be obtained for central files.

If the study drug is destroyed on-site, the investigator must maintain accurate records for all the study drug destroyed. Records must show the identification and quantity of each unit destroyed, the method of destruction, and the person who disposed of the study drug. Upon study completion, copies of the study drug accountability records must be filed at the site. Another copy will be returned to TLC.

The study monitor will review study drug supplies and associated records at periodic intervals.

#### **9.1.9. Inspections**

The investigator will make available all source documents and other records for this trial to TLC's appointed study monitors, to IRB/IEC, or to a regulatory authority or health authority inspectors.

#### **9.1.10. Protocol Compliance**

The investigator is responsible for ensuring the study is conducted in accordance with the procedures and evaluations described in this protocol.

## **9.2. Sponsor Responsibilities**

### **9.2.1. Protocol Modifications**

Protocol modifications, except those intended to reduce immediate risk to study subjects, may be made only by TLC. The investigator must submit all protocol modifications to the IRB/IEC in accordance with local requirements and receive documented IRB/IEC approval before modifications can be implemented.

### **9.2.2. Study Report**

A clinical study report will be prepared and provided to the regulatory agency(ies). TLC will ensure that the report meets the standards set out in the ICH Guideline for Structure and Content of Clinical Study Reports (ICH E3). Note that an abbreviated report may be prepared in certain cases.

## **9.3. Joint Investigator/Sponsor Responsibilities**

### **9.3.1. Payment Reporting**

Investigators and their study staff may be asked to provide services performed under this protocol (e.g., attendance at Investigator's Meetings). If required under the applicable statutory and regulatory requirements, TLC will capture and disclose to federal and state agencies any expenses paid or reimbursed for such services, including any clinical trial payments, meals, travel expenses or reimbursements, consulting fees, and any other transfer of value.

### **9.3.2. Access to Information for Monitoring**

In accordance with regulations and guidelines, the study monitor must have direct access to the investigator's source documentation in order to verify the accuracy of the data recorded in the CRF/eCRF.

The monitor is responsible for routine review of the CRF/eCRF at regular intervals throughout the study to verify adherence to the protocol and the completeness, consistency, and accuracy of the data being entered into them. The monitor should have access to any subject records needed to verify the entries on the CRF/eCRF. The investigator agrees to cooperate with the monitor to ensure that any problems detected through any type of monitoring (central, on-site) are resolved.

### **9.3.3. Access to Information for Auditing or Inspections**

Representatives of regulatory authorities or TLC may conduct inspections or audits of the clinical study. If the investigator is notified of an inspection by a regulatory authority the investigator agrees to notify the TLC MM immediately. The investigator agrees to provide representatives of a regulatory agency or TLC access to records, facilities, and personnel for the effective conduct of any inspection or audit.

#### **9.3.4. Study Discontinuation**

Both the sponsor and the investigator reserve the right to terminate the study at any time. Should this be necessary, both parties will arrange discontinuation procedures and notify the appropriate regulatory authority(ies), IRBs, and IECs. In terminating the study, TLC and the investigator will assure that adequate consideration is given to the protection of the subjects' interests.

## **11. APPENDICES**

- Appendix 1. Investigator Signature Page
- Appendix 2. Management of Clinical and Laboratory Adverse Events
- Appendix 3. Pregnancy Precautions, Definition for Female of Childbearing Potential, and Contraceptive Requirements
- Appendix 4. Common Terminology Criteria for Adverse Events (CTCAE) Grading Scale v5.0

## Appendix 2. Management of Clinical and Laboratory Adverse Events

---

[figure not shown]

### **Appendix 3. Pregnancy Precautions, Definition for Female of Childbearing Potential, and Contraceptive Requirements**

#### **1) Study Drug Effects on Pregnancy and Hormonal Contraception**

The risks of treatment with TLC-2716 during pregnancy have not been evaluated and reproductive and developmental toxicity studies have not been conducted. Clinical data regarding potential drug-drug interactions (DDI) between TLC-2716 and hormones used for contraception are not available. However, *in vitro* data suggest that TLC-2716 is an inducer of CYP3A4, which may affect the efficacy of hormonal contraceptives. Therefore, hormone-containing contraceptives should not be considered an effective form of contraception while used concurrently with TLC-2716. Pregnancy must be excluded before the start of treatment with the study drug and prevented thereafter by reliable, highly effective contraceptive methods. Pregnancy tests will be performed regularly throughout this study. Please refer to the latest version of the IB for additional information.

#### **2) Definition of Female of Childbearing Potential**

For the purposes of this study, a female-born subject is considered of childbearing potential following the initiation of puberty (Tanner stage 2) until becoming post-menopausal, unless permanently sterile or with medically documented ovarian failure.

Females are considered to be in a postmenopausal state when they are  $\geq 54$  years of age with cessation of previously occurring menses for  $\geq 12$  months without an alternative cause.

In addition, females of any age with amenorrhea of  $> 12$  months may also be considered postmenopausal if their follicle-stimulating hormone (FSH) level is in the postmenopausal range and they are not using hormonal contraception or hormonal replacement therapy.

Permanent sterilization includes hysterectomy, bilateral oophorectomy, or bilateral salpingectomy in a female subject of any age.

#### **3) Definition of Male Fertility**

For the purposes of this study, a male-born subject is considered fertile after the initiation of puberty unless permanently sterile by bilateral orchidectomy or medical documentation.

#### **4) Contraception Requirements for Female Subjects of Childbearing Potential**

The inclusion of female subjects of childbearing potential requires the use of highly effective contraceptive measures. Given potential drug-drug interactions involving TLC-2716, including with hormone-containing contraceptives, have not been evaluated, subjects must not rely solely on hormone-containing contraceptives as a form of birth control during the study.

Subjects must have a negative serum pregnancy test at Screening and a negative pregnancy test on Day -1 prior to randomization. In the event of a delayed menstrual period (over one month between menstruations), a pregnancy test must be performed to rule out pregnancy. This is also true for women of childbearing potential with infrequent or irregular periods. Female subjects must agree to one of the following methods of contraception from Screening until 30 days after the last dose of study drug:

- Complete abstinence from intercourse of reproductive potential. Abstinence is an acceptable method of contraception only when it is in line with the subject's preferred and usual lifestyle.

Or

Consistent and correct use of 1 of the following methods of birth control listed below:

- Intrauterine device (IUD) with a failure rate of < 1% per year
- Implant contraceptive
- Tubal sterilization (e.g., bilateral tubal ligation)
- Essure micro-insert system (provided confirmation of success 3 months after procedure)
- Vasectomy in the male partner (provided that the partner is the sole sexual partner and had confirmation of surgical success 3 months after procedure)

Or

Consistent and correct use of 1 of the following methods, in addition to use of a barrier method (male condoms, female condoms, or female diaphragm), as appropriate:

- Oral contraceptive
- Injectable contraceptive (e.g., Depo-Provera)
- Vaginal contraceptive ring

Note, barrier methods alone are not an acceptable form of contraception.

Female subjects must also refrain from egg donation and in vitro fertilization during treatment and until at least 90 days after the last dose of study drug.

## **5) Contraception Requirements for Male Subjects**

It is unknown if a relevant systemic concentration of the study drug could be achieved in a female partner from exposure to the male subject's seminal fluid. Therefore, male subjects with female partners of childbearing potential must use condoms during treatment and until 90 days after the last dose of study drug. Additional contraception recommendations should also be considered if the female partner is not pregnant.

Male subjects must also refrain from sperm donation during treatment and until at least 90 days after the last dose of study drug.

## **6) Unacceptable Birth Control Methods**

Birth control methods that are unacceptable include hormone-containing contraceptives, periodic abstinence (e.g., calendar, ovulation, symptothermal, post-ovulation methods), withdrawal (coitus interruptus), spermicides only, and lactational amenorrhea method (LAM). A female condom and a male condom should not be used together.

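### Appendix 3 contradicts itself on hormonal contraception: item 6 bars it without qualification, while item 4 accepts three hormonal methods with a barrier and an implant with none

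*Combined protocol and SAP*

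**What the plan says.** Three items of protocol Appendix 3 bear on hormonal contraception.

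- Item 6 (unacceptable methods): "Birth control methods that are unacceptable include hormone-containing contraceptives". No condition is attached. The same sentence does limit another method, adding the word only after spermicides.
- Item 4 (requirements for women of childbearing potential) sets a general rule: "subjects must not rely solely on hormone-containing contraceptives as a form of birth control during the study". It then gives the operative list: "Female subjects must agree to one of the following methods of contraception from Screening until 30 days after the last dose of study drug". Apart from abstinence, the list has two groups. In the first, one method is enough. That group includes "Intrauterine device (IUD) with a failure rate of < 1% per year" and "Implant contraceptive". The second group (oral, injectable, vaginal ring) carries a condition: "Consistent and correct use of 1 of the following methods, in addition to use of a barrier method". Item 4 adds: "Note, barrier methods alone are not an acceptable form of contraception".
- Item 1 (effects on pregnancy and hormonal contraception) says hormonal methods should not be counted as effective when used together with TLC-2716, because in vitro data suggest that it induces CYP3A4.

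Inclusion criterion 10 (Section 4.2) requires the methods described in Appendix 3. Exclusion criterion 10 (Section 4.3) and Section 5.5.1 exempt hormonal contraceptives from the medication restrictions, so women may enter and remain on them.

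**The concern.** A woman on the pill who also uses condoms meets item 4 and, on the face of item 6, is using an unacceptable method. A woman with an implant and no barrier is in the same position. Two staff members applying the appendix in good faith could reach opposite eligibility decisions.

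The question can readily arise. Roughly equal numbers of men and women are planned (Section 4.1), and hormonal contraceptives are permitted medication. The rule has a safety purpose: this is the first administration in humans, reproductive and developmental toxicity studies have not been done (Appendix 3, item 1), and TLC-2716 induced CYP3A4 more than 2-fold in human hepatocytes (Section 1.2.3). An implant is the most exposed case, because under item 4 nothing backs it up if induction reduces its efficacy.

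**Working it through.** The check sets the items side by side; the only arithmetic is a count. Item 4 offers nine options. The protocol does not say which of them contain hormone. The classification below uses the ordinary meaning of the names, for the oral, injectable and ring methods as much as for the implant. The IUD is taken as non-hormonal, since such a device satisfies both items.

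| Item 4 option | Hormonal (assumed) | Barrier required by item 4 | Against item 6 as printed | Against item 6 read as hormonal methods alone |
|---|---|---|---|---|
| Abstinence | no | no | consistent | consistent |
| IUD | no | no | consistent | consistent |
| Implant | yes | no | conflict | conflict |
| Tubal sterilization | no | no | consistent | consistent |
| Essure | no | no | consistent | consistent |
| Partner vasectomy | no | no | consistent | consistent |
| Oral | yes | yes | conflict | consistent |
| Injectable | yes | yes | conflict | consistent |
| Vaginal ring | yes | yes | conflict | consistent |

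1. As printed: 3 (oral, injectable, ring) + 1 (implant) = 4 of 9 conflict, and 9 − 4 = 5 satisfy both items.
2. Reading item 6 as hormonal methods alone: the three barrier-paired methods are reconciled, so 4 − 3 = 1 of 9 remains, the implant.
3. That remaining conflict is not only with item 6. A woman using just an implant relies solely on a hormonal method, which item 4's opening rule forbids, and item 1 says such a method should not be counted as effective during concurrent use.
4. Moving the implant to the group that requires a barrier: 1 − 1 = 0 conflicts between items 4 and 6.

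One tension lies outside this count. Read literally, item 1 gives the hormonal half of a pair no credit, so pill plus condom reduces to a barrier alone, which item 4 rejects. Whether the pairing is adequate is a medical question that the documents do not settle.

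Timing: item 4 applies until 30 days after the last dose. Discharge is Day 4 after a Day 1 dose, or Day 17 after a last dose on Day 14 (Sections 3.4 and 3.5), so 4 − 1 = 3 and 17 − 14 = 3 days. About 30 − 3 = 27 of the 30 days therefore fall outside the clinic.

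**The case against.** The best defence is that item 4 is the operative list and already shows what is meant. It forbids sole reliance on hormonal methods, then says how to pair them, and the medication rules allow them. On that view item 6 is loosely worded shorthand for hormonal methods alone. For the oral, injectable and ring methods this is the more natural reading and it stands. It does not rescue the implant, which item 4 accepts without the pairing that its own rule calls for.

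The defence can add that the documents never call the implant hormonal. That is so, but the same holds for the other three named methods; the inference is the ordinary one and is declared here as an assumption.

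A reader might infer that the rule cannot be followed at all. The documents do not support that: five of the nine options satisfy both items.

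A reader might also infer that women are exposed to a shown risk of pregnancy. That is not supported either. There is one centre, and subjects are confined on every dosing day. Pregnancy tests are scheduled at Screening, admission, discharge and follow-up. Item 1 speaks only of concurrent use, and nothing states how long induction lasts after the last dose. These facts limit the consequence. They do not remove the inconsistency, since item 4 applies from Screening and for about 27 days after discharge.

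**Conclusion.** The inconsistency is real and worth correcting. As printed, the eligibility status of 4 of 9 listed options is contradictory; on the most favourable reading of item 6, 1 of 9 (the implant) remains in conflict with item 4's own rule and with item 1. Adding a single word to item 6 is therefore not enough.

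This rests on the ordinary understanding that oral, injectable, ring and implant contraceptives contain hormone, and on taking the IUD as non-hormonal. The IUD entry is not counted as a conflict, but it needs clarifying because it does not exclude a hormonal device. The counts describe the list, not people: the documents do not say how many women would use these methods. The point concerns an eligibility rule with a safety rationale; it has no bearing on any endpoint, analysis or sample size.

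**What to change.** Amend Appendix 3 as follows.

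1. Item 4: move the implant to the group that requires a barrier, and state that an IUD used on its own must be non-hormonal.
2. Item 6: replace the unqualified entry with *hormone-containing contraceptives alone (without a barrier method)*.

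Leave the safety statement in item 1 as it is unless the medical team decides otherwise. Softening it would be a medical judgement, and item 1 itself notes that clinical interaction data are lacking. If the team holds that hormonal methods deserve no credit at all, the consistent alternative is to delete the hormonal options from item 4 and leave item 6 unqualified. Inclusion criterion 10 only points to the appendix and needs no change.

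The cost is a wording amendment. Some women would need to add a barrier or change method; under the stricter alternative, some would have to change method or would be ineligible.
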